### Eligibility Criteria

Individuals are eligible for inclusion if they 1) are over the age of 18, 2) have ever injected any non-prescribed drugs, 3) have used any non-prescription drugs within the past 12 months, and 4) are able and willing to provide informed consent. Participants will be excluded if they are unable or unwilling to provide informed consent in English or Swahili.

### Procedures

#### Brief Behavioral Survey

A brief behavioral survey will be administered to all participants in English or Swahili by study staff using computers. Domains in the survey include demographics, sexual risk behaviors, alcohol and drug use, IDU-related risk behaviors, and utilization of harm reduction services (Table 1).

#### Social Network Survey

All participants will also complete a social network survey that will provide information on their egocentric network. In this survey, participants will list up to 15 other PWID by name that they know and spend time with (e.g., family and friends, spouses or sexual partners, people that they purchase drugs from, people they inject drugs with, and ‘injection doctors’ (individuals located in injection venues who inject for others [55])) and provide information on their relationships and interactions with these individuals. This information relates to injection practices (date of last injection with this person, equipment and drug sharing); sexual behaviors (frequency of sexual contact, condom usage); and HIV, HBV, and HCV (testing and treatment status).

#### HCV Testing

After obtaining study consent and completing the behavioral survey, all participants without a recent (i.e., within the prior three months) HCV test result reported in the DIC registry will receive rapid HCV antibody testing (Abbott, Bioline HCV). Confirmatory viral load testing (Cepheid, GeneXpert) will be done at the National Public Health Laboratory in Nairobi for those who test HCV antibody positive. Participants undergoing confirmatory testing then return to the study site to receive their results, counseling, and referral to treatment. All testing procedures follow Government of Kenya standard of care [56]. For individuals with detectable HCV RNA, the sample will be used to perform next-generation sequencing (NGS) and phylogenetic analysis.

##### HCV Sequencing and Analysis.

Total nucleic acid (TNA) will be extracted from all specimens using 200 μl of plasma on KingFisher Pure Viral TNA Kit (Roche, Indianapolis, IN). Each RNA sample will be eluted in 50 μL of Elution Buffer and 21 μL will be subjected to DNA synthesis performed with one-step RT-PCR kit (Invitrogen, Thermo Fisher, Waltham, MA), targeting the hypervariable region (HVR1) of the HCV genome. Secondary Barcode nested PCR reactions containing unique 10-mer barcodes in both the reverse and forward HVR1 primers will be performed using PerfeCTa Reaction Mix (Quanta Biosciences, Beverly, MA). The amplicons will then be indexed with 8-mer indexes and adapters (IDT- Integrated DNA Technologies, Inc., Coralville, IA) appropriate for sequencing, clustering and demultiplexing on the Illumina MiSeq instrument (Illumina Biotechnology Company, San Diego, CA). The products will be purified using Ampure XP (Agilent Technologies), purity will be checked and quantified on Tape Station Instrument (Agilent Technologies, Santa Clara, CA). The quantified amplicons will be normalized and mixed to generate a 24 plex library including 2 negative controls. The library will be diluted to 10 pmol and sequenced using paired-end read protocol on Illumina MiSeq and v2 Nano chemistry. The library will be automatically de-multiplexed on the MiSeq instrument. Paired demultiplexed Illumina MiSeq output in form of FASTQ files will be uploaded onto the cloud-based portal called GHOST Global Health Outbreak and Surveillance Technology (GHOST) – Version 0.9.1 (cdc.gov), which provides a set of bioinformatics tools that apply quality control measures and analyze NGS data.

#### HIV Testing

All participants without a recent (i.e., within the prior three months) HIV test result reported in the DIC registry will also undergo rapid HIV testing conducted by study staff trained and certified in HIV counselling following NASCOP/Government of Kenya standards [57, 58]. Due to changes in Kenya’s testing guidelines [59], testing used Abbott Determine HIV-1/2 and Abbott First Response HIV-1/2 RDT kit for those with a reactive Determine test May 2022 to February 2025, and Trinscreen from March 2025 onward. Once results are ready, staff will inform participants of their results and conduct post-test counselling. The participants will be referred to the NSP site for appropriate HIV care referral.

#### HBV Testing

Anti-HBV rapid testing (Abbott, SD Bioline HBsAg) will also be provided to all enrolled participants without a recent (i.e., within the prior three months) HBV test result reported in the DIC registry. All tests will be conducted per recommended Kenyan National Guidelines for the Control and Management of Viral Hepatitis [56].

#### Positive Cohort Follow-Up

Participants who test HIV- or HCV antibody-positive at baseline or had a recent positive test recorded will undergo three follow-up visits at four-month intervals in the year following their baseline visit. Participants are given a one-month grace period before and after the four-month mark in which they can complete the visit. Participants who miss a visit are still eligible to complete later follow-up visits. Peer case managers at each site will assist study staff with recalling participants for their follow-up visits by conducting outreach at commonly frequented injection venues. At each of the three follow-up visits participants will complete biobehavioral and social network surveys with updated time frames, and will receive HIV, HCV, and HBV testing.

#### Negative Cohort Follow-Up

Due to resource limitations, it will not be possible to conduct multiple follow-ups for all participants. Following completion of the positive cohort follow-up visits, we will conduct one additional follow-up visit for individuals who test HIV- and HCV antibody-negative during their baseline visit to determine seroconversion with HIV, HCV, and/or HBV. Biobehavioral and social network data will also be collected during these follow-ups.

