### Study Population and Sampling

We will enroll up to 3500 PWID in Coastal Kenya, Nairobi, and the Western Region. Biometric data capture using iris scanners will be used to prevent double enrollment and to track repeat visits. Participants who test HIV-positive and/or HCV antibody-positive will be eligible to complete up to three follow-up visits in the year following their baseline visit. Additionally, participants who test HIV-negative and HCV antibody-negative will complete a one-time follow-up visit to assess for seroconversion. For each visit, participants will be compensated 400 KSH.

To perform RDS sampling, study and NSP staff will identify individuals who are highly socially networked to serve as seeds and begin peer recruitment chains. Between two and six initial seeds will be recruited from each NSP site. Potential seeds will complete a brief interview with study staff, after which seeds will be selected based on the number of other PWID they know and associate with, previous testing access and results, and length of time spent in each area/neighborhood. Once consented by research staff, these seeds will be instructed on how to recruit up to three eligible peers and offer them a coupon that allows study staff to track recruitment relationships. If the potential recruit approaches study staff with the coupon and expresses interest in participation, they will be screened and consented for the study. Potential recruits need not already be clients at the NSP site at which they redeem the coupon. Participants who recruit their peers will receive 100 KSH for each successful referral.

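### The negative-cohort rule omits participants whose baseline test was waived on a recent negative registry result: they either get no follow-up or enter with an infection status up to three months out of date

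*Protocol article*

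**What the plan says.** All passages are in the Methods of the protocol article unless noted.

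- **Who is tested at baseline.** HCV Testing covers "all participants without a recent (i.e., within the prior three months) HCV test result reported in the DIC registry". HIV Testing covers "All participants without a recent (i.e., within the prior three months) HIV test result reported in the DIC registry". HBV Testing covers "all enrolled participants without a recent (i.e., within the prior three months) HBV test result reported in the DIC registry". The waiver therefore works virus by virus.
- **Positive cohort.** Positive Cohort Follow-Up takes in "Participants who test HIV- or HCV antibody-positive at baseline or had a recent positive test recorded", so a registry positive qualifies without a study test. This cohort has "three follow-up visits at four-month intervals in the year following their baseline visit".
- **Negative cohort.** Negative Cohort Follow-Up takes in "individuals who test HIV- and HCV antibody-negative during their baseline visit to determine seroconversion with HIV, HCV, and/or HBV". A recorded negative result is not mentioned. The timing is "Following completion of the positive cohort follow-up visits, we will conduct one additional follow-up visit", with no interval given.
- **The same rule in Study Population and Sampling.** There, "participants who test HIV-negative and HCV antibody-negative will complete a one-time follow-up visit to assess for seroconversion". This gives neither a time point nor a registry clause.
- **Abstract, Methods.** Participants are to come back for one or more follow-up visits, without exception.
- **Additional Planned Analyses.** Cox models are planned for incident infection. No time origin is stated.

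**The concern.** The registry clause was written for one cohort and not for the other, which leaves two readings of the negative-cohort rule.

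On the literal reading, someone whose HIV or HCV test was waived on a recent negative did not test negative at the baseline visit. Unless positive for the other virus, that person falls outside both cohorts. People recently tested at a drop-in centre would then be missing from the group used to measure seroconversion.

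On the permissive reading they are admitted, but their negative status may date from up to three months before enrolment. An infection acquired in that gap is detected at follow-up and treated as new, although it came before the behaviour and network position that are meant to explain it. If time at risk also starts at enrolment, the event is counted while part of the exposed time is not.

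**Working it through.** **No figure to reproduce.** The article derives no event count or power figure from these rules. The check is a comparison of the rules, then the size of the effect.

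**Step 1: classify a participant whose test was waived.**

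- Registry positive for HIV or HCV: in the positive cohort by its registry clause.
- Registry negative for one virus, positive for the other: in the positive cohort through the other virus. Not excluded, but the dating problem applies to the virus with the waived test.
- Registry negative for one or both viruses, positive for neither: fails the positive rule, and fails the literal negative rule because at least one test was not done at the baseline visit. No follow-up, contrary to the Abstract.

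**Step 2: inputs if registry negatives are admitted.**

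- Age of the registry result, g: at most 3 months (testing sections). A mean of 1.5 months is an assumption (midpoint). The limit takes every result as exactly 3 months old.
- Follow-up from baseline, F: not stated for the negative cohort. Assumed 12 and 24 months.
- Incidence per 100 person-years (Additional Planned Analyses): HIV 2.5 and HCV 6.3 on the coast, 1.6 and 2.3 in Nairobi, below 1 in the Western region.
- Share of the negative cohort holding a registry result, s: not stated. Shown for 10% and 50%.
- Constant hazard: an assumption.

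**Step 3: share of detected infections that predate baseline, among registry negatives: g/(g+F).**

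- 12 months: 1.5/13.5 = 11%; limit 3/15 = 20%.
- 24 months: 1.5/25.5 = 6%; limit 3/27 = 11%.

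The exact form, (1 − exp(−λg))/(1 − exp(−λ(g+F))), gives 11.5% and 20.6% for coastal HCV at 12 months, so the approximation is adequate.

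**Step 4: expected infections in the gap per 1,000 registry negatives: 1 − exp(−λg), for g = 1.5 to 3 months.**

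- Coast: HCV 7.8 to 15.6, HIV 3.1 to 6.2.
- Nairobi: HCV 2.9 to 5.7, HIV 2.0 to 4.0.
- Western region: at most 1.3 to 2.5.

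**Step 5: rate inflation among registry negatives, only if time at risk starts at enrolment: g/F.**

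- 12 months: 1.5/12 = 12.5%; limit 3/12 = 25%. Coastal HCV of 6.3 would appear as 6.3 × 1.125 = 7.1; limit 6.3 × 1.25 = 7.9.
- 24 months: 1.5/24 = 6%; limit 3/24 = 12.5%.

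If time at risk starts at the registry test, the inflation is zero. The share in Step 3 still precedes the baseline measures.

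**Step 6: inflation over the whole negative cohort at 12 months, same condition: s × g/F.**

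- s = 10%: 0.10 × 12.5% = about 1%; limit 0.10 × 25% = 2.5%.
- s = 50%: 0.50 × 12.5% = about 6%; limit 0.50 × 25% = 12.5%.

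**The case against.** The strongest reply is that the literal exclusion is a drafting slip. Study Population and Sampling states both cohort rules without any registry clause, even for positives, so the article uses testing positive or negative loosely. Negative Cohort Follow-Up also explains the single visit by limited resources, which suggests one visit for those outside the positive cohort rather than none. That is plausible, and nothing shows an intent to drop registry negatives. But if they are meant to be in, the dating problem follows, so calling it a slip moves the difficulty without removing it.

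A second reply is that time origin is commonly left to an analysis plan, which is not at hand. This stands. A reader might infer that the incidence rates will be inflated; the article does not support that, because it never says where time at risk starts. The temporal-order problem does not depend on that choice.

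Other stronger readings should also be resisted:

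- **Larger shares at a four-month visit.** The same formula gives 1.5/5.5 = 27% (limit 3/7 = 43%). Only the positive cohort has such a visit, so these figures apply only to someone positive for one virus and registry negative for the other, and only to infections found at that first visit.
- **Bias in the centrality comparisons.** This requires recent registry testing to be related to centrality. Seeds are chosen partly on connectedness and on previous testing access and results, so a link is possible, but none is shown.
- **Twelve months as typical.** The negative-cohort visit follows completion of the positive-cohort visits, which take about a year, so 12 months is near the short end and the effect shrinks with longer follow-up.

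Finally, incidence modelling is an additional analysis. The primary aim is to characterise networks and identify highly central people.

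**Conclusion.** The point holds in limited form. The waiver and the mismatch between the two cohort rules are in the text, and the literal negative rule conflicts with the Abstract's return visit for everyone. If registry negatives are admitted, roughly one in nine of their detected infections at 12 months, and at most one in five, would predate baseline; this roughly halves at 24 months. These shares rest on a constant hazard and on the assumed age of registry results and length of follow-up. Any rate inflation is conditional on starting time at risk at enrolment, and its size over the whole cohort depends on a registry share that the article does not give. Comparisons by service use or centrality can be biased if registry testing is related to them. The effect is modest and confined to the incidence analysis, but neither reading is satisfactory as written.

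**What to change.** 1. **Eligibility.** Reconcile Study Population and Sampling, Positive Cohort Follow-Up and Negative Cohort Follow-Up, so that the negative cohort is everyone negative for both HIV and HCV antibody, either at baseline or on a recent registry result.
2. **Time at risk.** For each infection, start at the date of the last negative test, whether registry or study.
3. **Sensitivity analysis.** Repeat the incidence models without infections whose interval from last negative to first positive spans enrolment, or restrict them to participants tested negative at baseline. In the negative cohort the restriction is cleaner: with a single follow-up visit, every infection found in a registry negative spans enrolment, so dropping the infections alone would leave their person-time without events.

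The cost is one clause and recording the registry test date, which sites must already consult to apply the three-month rule. The sensitivity analysis has fewer events, roughly in proportion to the share holding a registry result. Items 2 and 3 remain possible after enrolment closes if that date can be retrieved. Testing registry negatives at baseline is optional: it would resolve the exclusion and most of the dating problem, but not the window period of the antibody test.

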#### Qualitative Survey

A qualitative survey will be conducted to elicit knowledge, attitudes, and behaviors regarding HCV and associated risk factors among participants found to be highly networked and among participants who report frequenting “base camps” or “dens.” Approximately N=40 participants will be interviewed. Trained staff will audio-record the interviews, which will then be transcribed. Transcripts will then be imported into Dedoose software (Hermosa Beach, CA) for coding and analysis. These interviews will expand upon quantitative data related to social network composition and reported risk behaviors. Additionally, they will provide insight into the acceptability and feasibility of targeting these individuals for HCV treatment and leveraging them to provide PWID-focused HCV and HIV harm reduction education and services.

The survey instrument will be semi-structured and designed using the Rhodes Risk Environment Framework [60, 61] as a theoretical framework. Key informant interviews with PWID who are determined to be highly central in injection networks will be used to enhance information about HCV as well as HIV transmission and prevention. The social and cultural environment could affect the use of prevention practices, which are often mediated by key factors such as stigma, violence, and discrimination. Peers and norms are also external factors that could influence knowledge, attitudes, and behaviors. Lastly, economic factors could prevent changes in practice of harm reduction, as many PWID may not have the resources for transportation to seek clean needles at NSPs and may turn to injection doctors or other sources. These characteristics will be determined in qualitative interviews and applied to theories of behavioral change to ascertain how to create interventions that will successfully lower the risk of HIV and HCV infection/re-infection.

### Ethical Considerations

This study was approved by the Albert Einstein College of Medicine Institutional Review Board (IRB# 2021–12928) and the Kenyatta National Hospital Ethics and Research Committee (ERC; University of Nairobi; IRB# P856/10/2021). Formal informed consent will be obtained from all study participants and participation is strictly voluntary.

### Network Analyses

We will use three layers of network data to characterize the networks of PWID enrolled in our study: 1) Recruitment network, 2) Phylogenetic network, 3) Egocentric network.

#### Recruitment network

RDS network data are restricted by the RDS tree-based structure, which will look similar regardless of the degree of clustering in the network. RDS data alone therefore provide little network information as only ties used for recruitment are observed in the data. While it is possible to make inference about clustering based on homophily on observable characteristics (e.g. are infected population members more likely tied to other infected population members?) [62], it is not possible to infer endogenous clustering – the inherent tendency in social networks for friends-of-friends to be friends. Nonetheless, such clustering is an important feature of disease transmission in networks.

We will use token data to make inferences about the presence and extent of endogenous clustering in these social networks. We will also use this data to infer network structures and compare them to information available in this dataset, but difficult to collect elsewhere, including the distance of GHOST sequence information, and direct reports of social networks. We anticipate this token approach will provide a practical low-cost method to improve the availability of disease-relevant information in RDS data. Token data will also give more complete data from which to estimate network centrality. We will measure degree, closeness, and eigenvector centrality on these RDS coupon and token observed network data to compare to other critical nodal features as well as to centrality based on the other network data sources.

#### Phylogenetic network

NGS will be applied to the HVR1 of the HCV genome to perform phylogenetic analysis for participants with chronic HCV. HVR1 is the most variable and thus the most commonly used in molecular epidemiologic studies to detect clusters of persons infected via transmission events [63]. To visualize linkages in detail, all haplotypes with frequency >2 will be used to generate alignments using CLC Genomics Workbench v11 (QIAGEN Aarhus A/S). The patristic distances (i.e., genetic distance between two sequences in a phylogenetic tree measured in nucleotide substitutions per site) included the pairwise intra-person (two sequences from one individual) and the within-genotype inter-person (two sequences from two different individuals) distances. Cutoffs to phylogenies will be assigned using the intra-person distances, and sequences from different individuals with patristic distances falling below these cutoffs will be interpreted as transmission pairs or clusters. A transmission network that represents the genetic relatedness among HCV in participants will be built using the CDC developed web-based (https://webappx.cdc.gov/GHOST) GHOST, hosting a sequence cleaning algorithm for HVR1 NGS data, and the threshold method for detection of HCV transmission [63].

#### Egocentric network

For further network analysis, egocentric social network data collected through the social network surveys will be analyzed using a probabilistic linkage model. This analysis will allow for examination of differences between RDS/token networks and self-reported social networks, potentially identifying individuals that were missed by the RDS process.

### Additional Planned Analyses

Baseline and follow-up demographic and clinical information will be used to assess demographic, behavioral, structural, virologic, and geographic risk factors associated with positions of high centrality; additionally, we will assess associations between centrality measures and HIV, HCV, and HBV disease status. To assess centrality, we will create a unified network using egocentric social network data, RDS data, and token data; and use results from the GHOST analysis to examine how transmission occurred within these other networks. Tabular analysis will be used to explore bivariate associations between these characteristics, risk behaviors, and the presence of HIV/HCV co-infection or multiple-strain HCV infection. Factors strongly associated with having high centrality with *p*-values less than 0.2 will be considered for inclusion in multivariable models. Because RDS sample is not a random sample, we will conduct weighted regression analyses by using RDS weights, which are calculated as inverse of self-reported network size [64].

To evaluate the effect of having high centrality on transmission and acquisition of blood borne infections, cox proportional hazard models (adjusting for host demographic, risk behavior and clinical factors) will be used to estimate the hazard ratios for associations between HIV/HCV co-infection, multiple-strain infection, and other factors associated with having high centrality on the probability of incident blood borne infections. Incidence rates per 100 person-years of HIV and HCV were estimated to be 2.5 and 6.3 in the coastal region, 1.6 and 2.3 in Nairobi, and less than 1 in the Western region, based on previous data [12].

Individual transmission events defined through GHOST will also be studied to investigate factors associated with directionality of HCV transmission. A global meta-analysis of the prevalence of HIV, HCV, and HBV among PWID showed that HIV was more prevalent among women who inject drugs in some regions, including Sub-Saharan Africa [65, 66]. Participants from another qualitative study reported that individuals in drug dens referred to as “injection doctors” may play a role in unsafe injections and could be highly central vectors of transmission [55]. Specific details of these relationships warrant further investigation and will be explored through qualitative interviews. Additionally, if there are other phenomena that fall outside of the models, in-depth qualitative analysis will be conducted to further elucidate these factors.

Intra-host viral heterogeneity via NGS will be utilized to estimate the duration of time since transmission, enabling the outlining of temporal trends of where initial HCV infections were established and the way in which PWID have migrated over time [67]. Understanding migration patterns leading to movement inland may help to prevent further transmission in the Western region, which has thus far been relatively unaffected by HCV. This understanding of PWID migration may also be useful in informing HIV treatment and prevention efforts.

Lastly, an agent-based model of the transmission of HIV and HCV among PWID will be developed in the Python programming language. The model will be calibrated to the behavioral and social network surveys, disease statuses, and previously published population level data. By reproducing the structural and dynamical properties of the network of injecting partnerships, the model will replicate the disproportionate role that some individuals play in the transmission of disease. The model will be used to predict the impact of different strategies to target interventions (e.g. HCV/HIV test and treat, OAT and NSP).

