## Limitations

The assertion that individuals who are highly central will be at high risk of receiving and transmitting HIV, HCV and other BBIs may not be evident in this population of PWID. Moreover, the association of HIV/HCV co-infection, multiple-strain HCV infection, or other factors may not be able to be demonstrated in this sample due to sample size constraints. Additionally, though we believe RDS to be the best sampling method for this work, it may also introduce some bias to the study. For example, though RDS assumes recruiters will pass their coupons and tokens to network contacts, it is possible that they may pass the coupon off to a stranger (e.g., someone visiting the NSP site at the same time). Coupon distribution behaviors (e.g., who is approached, why and how they are approached, who accepts and why they accept) may also vary between individuals, leading to undocumented variation. In highly clustered populations, it is also possible that the RDS sample will not mix well and draw from the full target population with the expected proportions. This could lead to undue influence of the seeds on the final sample. This method of recruitment by referral also naturally biases selection towards individuals with a larger number of contacts. Individuals with no contacts will not be represented in the sample. Additionally, given that each referral chain starts at a single location, the geographical distribution cannot be expected to be representative of the whole population of PWID. PWID living close to a seed location are more likely to be included. Additionally, those living far away from an NSP site may be less likely to return a coupon.

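### Geographic factors are tested against a centrality measure built partly from ties whose recording depends on access to a study site, so site access can be mistaken for network position

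*Protocol article*

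**What the plan says.** All references are to the Protocol article.

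- **Analysis.** Under Additional Planned Analyses, the data are to be "used to assess demographic, behavioral, structural, virologic, and geographic risk factors associated with positions of high centrality". The Study Objectives also list geographic risk factors for high centrality.
- **Network.** The same section states: "To assess centrality, we will create a unified network using egocentric social network data, RDS data, and token data". The Recruitment network section adds a coupon-and-token version: "We will measure degree, closeness, and eigenvector centrality on these RDS coupon and token observed network data".
- **How ties arise.** Under Study Population and Sampling, each recruiter has up to three coupons, which recruits redeem at an NSP site. Up to five baseline tokens go to people already enrolled, and the brief survey and payment follow redemption. In the Social Network Survey, "participants will list up to 15 other PWID by name that they know and spend time with". No visit by the named person is needed.
- **Use of the survey layer.** Under Egocentric network, "egocentric social network data collected through the social network surveys will be analyzed using a probabilistic linkage model", with the stated benefit of "potentially identifying individuals that were missed by the RDS process".
- **Acknowledged selection.** Limitations says that people living near a seed location are more likely to be included, and that "those living far away from an NSP site may be less likely to return a coupon".
- **Stated weighting.** Regressions use weights equal to the inverse of self-reported network size.

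**The concern.** The article names a process by which distance may affect who enrols and which coupons come back. It treats this as a question of representativeness. The same process also determines which ties are seen, and those ties feed the outcome of the geographic analysis. If a participant's contacts tend to live in the same area, a participant far from a site has fewer recorded ties than an equally connected participant close to one.

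The study is meant to inform targeting of highly central people, and the Introduction raises venue-based intervention. An artefact of this kind would favour areas around the study's own sites and make distant injecting areas look poorly connected.

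**Working it through.** The documents give no redemption or enrolment rate by distance, so there is no figure to reproduce. All rates below are assumptions. The coupon, token and naming limits (3, 5 and 15) come from the article.

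**Step 1. Which ties depend on attendance**

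| Tie | Needs attendance or enrolment by the contact? |
|---|---|
| Coupon | Yes, redemption at an NSP site |
| Token | Yes, the contact must be enrolled and redeem |
| Contact named by the participant | No |
| Nomination received from someone else | Yes, that person must be enrolled |
| Onward ties of a named contact | Yes, the contact must be enrolled |

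Degree, closeness and eigenvector centrality on the unified network all draw on some of the dependent rows.

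**Step 2. Expected coupon and token ties with equal true degree**

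Assume a true degree of 15 for everyone, 80% of contacts in the same distance group, and redemption of 0.6 near and 0.4 far. Each person gives out 3 + 5 = 8 coupons and tokens, has one recruiter tie and is offered 5 tokens on average.

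- Near: contact redemption = 0.8 × 0.6 + 0.2 × 0.4 = 0.56. Expected ties = 8 × 0.56 + 1 + 5 × 0.6 = 8.48.
- Far: contact redemption = 0.8 × 0.4 + 0.2 × 0.6 = 0.44. Expected ties = 8 × 0.44 + 1 + 5 × 0.4 = 6.52.

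The simulation gave 8.49 and 6.51. Recorded degree is about 23% lower far from a site (1 − 6.52/8.48 = 0.23), although true degree is identical. The odds ratio for being in the top quartile was 6.7, or 3.2 with a true degree of 8. These show direction and should not be read as a likely size, because everyone has exactly the same true degree and little else separates people. If every named contact is kept, this set-up gives 1.0 by construction, because it gives each person the full true degree.

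**Step 3. A fuller network**

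Assume 4 sites with 2,000 people each, varying true degree (mean about 12) with the same distribution near and far, and 70% of ties within zone. Participants name 70% of their contacts, up to 15, and nominations received are included. High centrality is the top decile, with 20 replicates. The strong gradient is enrolment of 12% versus 7.5% and redemption of 80% versus 60%.

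Ignoring size-biased enrolment, the share of contacts enrolled is 0.7 × 12 + 0.3 × 7.5 = 10.65% for a near participant and 0.7 × 7.5 + 0.3 × 12 = 8.85% for a far one. Near-versus-far odds ratios (truth about 1.0):

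| Network, strong gradient | Degree | Closeness | Eigenvector |
|---|---|---|---|
| Token only | 2.4 | – | – |
| Unified, matched contacts only | 2.0 | 2.0 | 2.2 |
| Unified, all named contacts kept | 1.4 | 1.6 | 2.1 |

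With a mild gradient (10.5% versus 9%; 80% versus 75%) the values were 1.1 to 1.4. With none they were 0.86 to 1.02. A further simulation with equal true degree and a strong assumed gradient gave about 2.8, 2.1 and 1.4 for the three degree entries, 1.1 to 1.3 under a mild gradient and about 1.0 with none. In it, the participant's own named count stayed at about 1.0.

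**Step 4. Weights**

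A participant reporting 12 contacts has weight 1/12 near or far. Distance changes the share of ties recorded and leaves the reported size unchanged, so the weights cannot separate the groups. In the further simulation, weighting did not help.

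**The case against.** A reader might infer that every tie in the network requires the contact to come to a site. The documents do not support that. The unified network includes survey-named ties, and if all named contacts are kept the distortion in degree is much smaller. The article leaves the handling of unmatched contacts open, as a condensed article may.

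A reader might also infer that the plan would present proximity to a site as a cause of centrality. It speaks only of association. Nor does it define geographic factors as distance to a site. They may mean region or injection venue, and then the distortion needs access to differ between areas, which the documents do not show.

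The remaining objections are these:

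- The distance caveat is stated for coupons. A gradient in token redemption is an assumption, although tokens still require an enrolled contact.
- The plan already compares coupon-and-token networks with self-reported ones, and centrality across data sources. It does not tie these comparisons to the geographic models.
- Multivariable models are planned, and Table 1 lists location and travel at visits 0 to 3, so adjustment for distance is not excluded.
- Making a self-reported count the main outcome would replace the study's centrality aim with a degree measure.

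These points limit the size and the remedy. They do not remove the dependence of recorded ties on enrolment and redemption, or its absence from the geographic analysis.

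**Conclusion.** The concern holds as a risk of spurious association. Coupon and token ties, nominations received and the onward ties of named people depend on enrolment or redemption. The article itself says that inclusion and coupon return may fall with distance, and the stated weights carry no distance term.

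The size cannot be fixed from the documents. With equal true degree, the near-versus-far odds ratio is about 1.0 with no gradient. For degree under a strong assumed gradient it runs from about 1.4 (all named contacts kept) to about 2.8 (token ties only). This rests on the assumed enrolment and redemption rates and on contacts being geographically clustered.

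It does not follow that unified-network centrality should be dropped or demoted. A cheap additional analysis, with a stated limit on interpretation, is enough.

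**What to change.** Under Additional Planned Analyses, keep unified-network centrality as the main outcome and add the following for the geographic factors:

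1. Repeat the models with a redemption-free outcome: the number of people the participant names in the social network survey, or self-reported network size. The named count is easier to use in the weighted models, because self-reported size is also the denominator of the weight.
2. Repeat the models with distance or travel time from residence to the study site added, where the location data allow.
3. If a geographic association is absent on the redemption-free measure, report it as possibly due to site access and not as evidence of where central people are.
4. Link the distance caveat in Limitations to this analysis.

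The cost is a few sentences and extra models on data already collected. The redemption-free measure captures degree only, so it cannot stand in for closeness or eigenvector centrality. It is also noisy, and the named list stops at 15. Adjusting for distance can absorb a real effect of living near a site. For these reasons both serve as checks beside the main analysis.
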